## 6. DATA COLLECTION AND PROCESSING

#### *6.1 Measuring outcomes*

Outcomes are measured at 6, 12 and 18 weeks post randomisation. The primary outcome is the volume of UI leaked in 24 hours at 6 weeks post randomisation, as measured by a 24-hour pad weight test (PWT)37. Pad weight tests at 12 and 18 weeks measure the sustainability of any effect. The test is based on the premise that 1g fluid weight = 1 ml urine and is thus an objective measure of urine leakage. The PWT involves the resident emptying their bladder, applying a clean, dry pad at an agreed set time and retaining all pads used between this time and 24 hours later. To maintain the moisture in the removed pads and prevent evaporation all collected pads are individually sealed in a small plastic bag and then placed in a larger re-sealable bag, which is weighed on site by the RRA after the 24-hour collection ends. The dry weight of the equivalent pads to those collected is deducted from the total weight to provide the 24-hour volume of UI leaked.

Secondary OCM include the *number of pads used in 24 hours*, which may be expected to reduce if TPTNS is effective in reducing volume of UI and will be reflected in the economic evaluation*.*

*Post void residual urine volume* (PVRU) is measured using a non-invasive portable ultrasound bladder scanner. Our pilot study conducted with CH residents1 suggested a potential mean decrease of 55ml in PVRU following a TPTNS programme compared to the sham stimulation group, it is thus worth investigating whether this was an artefact, or whether TPTNS impacts on urinary retention in the frail older adult population. Additionally, it is important to ensure that any effect of TPTNS in reducing bladder leakage is not as a result of an increase in retained urine volume.

The *Patient Perception of Bladder Condition* (PPBC) is a single question global patient reported outcome measure of perceived bladder condition with six possible responses ranging from ‘My bladder condition does not cause me any problems at all’ to ‘My bladder condition causes me many severe problems’. It has good construct validity and responsiveness to change38 and is recommended as a global outcome measure for UI39. It is used at each time point with residents. However, it has also been adapted in this study for use by family carers (FC-PBC) and CH staff (S-PBC) to offer a perspective on how they believe the resident feels about their bladder condition.

The *Minnesota Toileting Skills Questionnaire* (MTSQ) is a five question patient reported outcome measure of degree of difficulty on a scale of 0 to 4 completing five tasks involved in toileting. Scores range from 0 to 20, with higher scores indicating more difficulty. The MTSQ is a reliable and valid interviewer administered measure of toileting skills in physically frail older women65. It is completed at all timepoints by the resident and staff member.

Quality of life is measured using the *DEMQOL and DEMQOL-Proxy*40, valid and reliable measures of health-related quality of life in people with dementia. The DEMQOL-Proxy is completed by a single identified proxy for the resident. Both measures are completed at the primary outcome point (6 weeks post randomisation) and at the 18 week follow up assessment.

Economic evaluation is undertaken using routine data available in CHs as well as information from the Resource Use Questionnaire (RUQ) on which the RRA records at baseline the usual continence care pathway including details on usage of pads, medication which may affect continence, and (if appropriate) number of staff required to assist the resident to use the toilet. At the follow up time points, in combination with the 24 hour bladder diary, the RRAs use this questionnaire to update the continence care pathway. If residents have required any care from health professionals external to the CH as a result of their UI, this is also recorded on the RUQ.

Table 1 (below) summarises what outcomes are assessed at baseline, 6-week, 12-week and 18-week post randomisation assessments.

**Table 1**

|  | **Baseline** | **6-week** | **12-weeks** | **18weeks** | Data collector |
| --- | --- | --- | --- | --- | --- |
| 24 hour PWT | ● | ● | ● | ● | CH staff  RRA |
| Number of pads used | ● | ● | ● | ● | RRA |
| 24 hour bladder diary | ● | ● | ● | ● | CH staff |
| PVRU | ● | ● | ● | ● | RRA |
| PPBC | ● | ● | ● | ● | Resident and RRA |
| FC-PBC | ● | ● | ● | ● | Family member |
| S-PBC | ● | ● | ● | ● | SC/RN responsible for care provision |
| MTSQ | ● | ● | ● | ● | Resident and RRA |
| MTSQ | ● | ● | ● | ● | CH staff and RRA |
| DEMQOL | ● | ● |  | ● | Resident and RRA |
| DEMQOL-proxy | ● | ● |  | ● | Single, named proxy and RRA |
| Resource Use Questionnaire | ● | ● |  | ● | RRA |

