***Sham stimulation*** comprises low intensity, sub-clinical stimulation of the lateral sub-malleolar area, positioned specifically on the lateral aspect to avoid the tibial nerve, which runs close to the skin surface behind the medial malleolus. The stimulation parameters are identical to the TPTNS stimulation other than the intensity of the current which will be set at 4mA, rather than adjusted individually as it is in the TPTNS intervention group. The current will be initially increased until the resident reports feeling some sensation following which the current will be reduced down to 4mA. All residents will be informed that they may not feel anything with this intervention and that this is quite normal.

Both intervention and sham groups will receive an electrical stimulation intervention comprising a total of 12 sessions of 30 minutes duration each, delivered twice weekly over 6 weeks. The intervention equipment and method of delivery are identical in everything but the intensity of electrical stimulation and the positioning of the surface electrodes. The electrical stimulation programme for all residents will be 10Hz frequency, 200μs pulse width, delivered in continuous stimulation mode. The electrical stimulators will be programmed to the set parameters and locked prior to individual use so that the only adjustable parameter will be the intensity of stimulation. The intervention will be delivered by CH registered nurses and senior carers who will receive specific training and support to undertake this role. Fidelity of delivery of the intervention and sham stimulation will be monitored.

No strict TPTNS/sham intervention timetable will be set and individual CHs will have flexibility around where, how and when they deliver the sessions, bearing in mind that they must occur twice weekly for 30 minutes each over a 6-week period. A proposed schedule for each home and resident will be agreed between the resident, registered nurse/senior carer and local PI at the point of treatment inception.

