**3.2 Strategies to monitor adherence to intervention**

An individual resident stimulation diary is completed by the registered nurse/senior carer after delivering each session. It records date, time, intensity of electrical stimulation and any comments on the process of delivering the intervention. The locked stimulation machines automatically record the total stimulation time in use and the average stimulation intensity, thus an objective record of the stimulation programme provided to each resident is recorded, which is compared against the individually recorded stimulation diary. Electrode positioning by staff to deliver the intervention/sham stimulation will be recorded using a digital photograph taken by staff every two weeks during the intervention delivery time.

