**4.5 Randomisation and allocation**

Following consent, baseline data will be collected. Only once all baseline data are recorded will remote randomisation be initiated. Eligible and consenting residents are randomised to one of the two groups (TPTNS or sham) using the proven 24-hour telephone Interactive Voice Response randomisation application or via the web-based application (and phone, if appropriate), both hosted by CHaRT. Information required to perform the randomisation is submitted by the RRA, who has obtained the consent, however to ensure the RRA is blinded to group allocation the information on the allocated group is delivered to the local PI in each CH by the ELECTRIC trial office, who receive the allocation information from CHaRT. The local PI records the allocated group in a separate file and informs the CH staff who will deliver the allocated intervention.

Randomisation will be computer allocated on a one to one basis in random permuted blocks of size two, four or six, with stratification by:

- Sex – male/female
- UI severity - mild (0-200ml/24 hrs); moderate (200-400ml /24 hrs); severe (400+ ml/24 hrs)
- Centre

**4.6 Administration arrangements post recruitment** (if applicable)

Following recruitment, the following administration arrangements will be undertaken:

- The Trial Office will notify the resident’s GP/medical practitioner in writing that the resident has joined the trial.
- The RRA will file a copy of the consent form in the resident’s care notes along with information about the trial.
- The RRA will file a copy of the GP/medical practitioner letter in the resident’s care notes.
- The RRA will enter trial data regarding the resident into the bespoke trial website.
- The RRA will maintain trial documentation at each site in their region (Scotland or England).
- The RRA will return a copy of the signed consent form to the Trial Office in Glasgow.

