**6.6 Data processing**

Paper based and electronic data entry will be used. RRAs enter locally collected data to the database in the CHs for screening and randomisation purposes. Paper based CRF data will be delivered securely to the Trial Office for data entry. Staff in the Trial Office work closely with local RRAs to ensure the data are as complete and accurate as possible.

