**7.3 Procedures for detecting, recording, evaluating & reporting AEs, SAEs**

**7.3.1 Detecting AEs and SAEs**

All AEs and SAEs meeting the criteria for recording within the ELECTRIC trial (see section 7.2) are recorded, from the time a participant consents to join the trial until the last trial follow-up. The RRA asks the participant/proxy (consultee [England], welfare attorney/nearest relative [Scotland]) or CH staff delivering the TPTNS/sham intervention about the occurrence of relevant AEs (i.e. those that meet the criteria for recording within the ELECTRIC trial) at each follow-up data collection point. AEs are also recorded in the stimulation diary.

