### *Assessment of Seriousness*

### The local PI / RRA / CI will make an assessment of seriousness as defined above.

### *Assessment of Relatedness (causality)*

The CI / RRA will make an assessment of whether the AE is likely to be related to research procedures according to the following definitions:

- **Related**: resulted from administration of TPTNS or sham stimulation or the outcomes data collection processes.
- **Unrelated**: where an event is not considered to have resulted from any of the research procedures.

Alternative causes such as natural history of any underlying disease, concomitant therapy, other risk factors and the temporal relationship of the event to the treatment are considered.

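### The research assistant's blinding is stated but not protected by the adverse event procedures, and the staff-rated outcomes and pad collection rest on care home staff who may know the allocation

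*Protocol*

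**What the plan says.** **Blinding.** Section 4.5 has the RRA submit the randomisation details, but "to ensure the RRA is blinded to group allocation the information on the allocated group is delivered to the local PI in each CH". The local PI then tells the staff who will deliver the treatment. Section 4.7 adds that the sham keeps residents and relatives blind. Nothing is claimed for care home staff.

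**Outcomes.** The RRA weighs the bagged pads on site (Section 6.1) and counts them. Table 1 also gives the RRA the resident interviews: PPBC, MTSQ and DEMQOL. Care home staff are listed with the RRA for the 24-hour pad test and for the staff version of the MTSQ. S-PBC comes from the "SC/RN responsible for care provision".

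**Delivery.** Section 3.1: "The intervention will be delivered by CH registered nurses and senior carers who will receive specific training and support to undertake this role". Each session goes into a stimulation diary (Section 3.2): "It records date, time, intensity of electrical stimulation and any comments on the process of delivering the intervention".

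**Adverse events.** Under Section 7.3.1 the RRA, at each follow-up, asks the participant or proxy, or "CH staff delivering the TPTNS/sham intervention about the occurrence of relevant AEs". Events are also written in the stimulation diary. Section 7.3.2 makes the local PI, the RRA or a delegate responsible for reviewing care home records of an event. On causality, Section 7.3.3 says: "The CI / RRA will make an assessment of whether the AE is likely to be related to research procedures".

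**The concern.** The protocol goes to some trouble to keep the RRA blind, then gives the same person three safety tasks that can each disclose the arm. It states no safeguard at those contacts. This matters most for PPBC, MTSQ and DEMQOL, where the RRA conducts the interview. It matters less for the pad weight, which is objective once the bag is on the scale.

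The second strand concerns care home staff. S-PBC is a single-item rating of how staff believe the resident feels, and the staff MTSQ is also a rating. Both may come from people who know the arm. The baseline ratings are made before randomisation and the follow-up ratings after it, so adjusting for baseline cannot remove a bias that starts with knowledge of the arm.

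The primary outcome is exposed at collection. Dry weight is deducted only for the pads that were collected, and no reconciliation with pads issued is described. A pad that is not kept therefore lowers the measured leakage, and weighing by the RRA cannot detect it. Toileting on the test day is also in staff hands.

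**Working it through.** **Step 1. Can the RRA's safety tasks reveal the arm?**

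| Task open to the RRA | Where | What can disclose the arm |
| --- | --- | --- |
| Ask delivering staff about events at each follow-up | 7.3.1 | Those staff know the allocation (4.5) |
| Review care home records of an event | 7.3.2 | Events are also in the stimulation diary (7.3.1), which shows intensity (3.2). Sham is set at 4mA; TPTNS is adjusted individually (3.1) |
| Judge relatedness | 7.3.3 | Expected events are redness and itch at the electrode sites (7.2). Electrodes are medial in TPTNS and lateral in sham (3.1) |

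Each route is possible and none is certain. Section 7.3.1 joins its sources with *or*, and asking about an event does not by itself reveal the arm. Section 7.3.2 does not say that the RRA opens the diary. The protocol does not say whether events are asked about before or after the outcomes are recorded. What Section 4.5 sets out to secure is therefore left to chance in Section 7.3.

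**Step 2. Do raters and deliverers overlap?** Registered nurses and senior carers deliver the stimulation, and the S-PBC rater is drawn from the same two grades. Homes may have as few as 25 residents (Section 9.2). Overlap is likely and nothing excludes it, but it is inferred from grade. The protocol does not state it.

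**Step 3. Scale, starting from the protocol's own figures (Section 9.1).** Inputs: difference 200 ml, SD 570 ml, two-sided alpha 5%, power 90%, 1:1 allocation.

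- Effect size: 200/570 = 0.351, stated as 0.35.
- n per arm = 2(1.960 + 1.282)²/0.35² = 171.6, rounded up to 172, so 344 in total, as stated.
- Attrition: 344/0.70 = 491.4, rounded up to 492, against 500 planned (500 corresponds to 1 − 344/500 = 31.2%).

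The sample size is reproduced and this point does not affect it.

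**Step 4. Illustration on assumed values that are not in the protocol.**

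- Suppose a pad holding 100 to 200 ml went unbagged in 20 percentage points more residents of one arm. The artefact is 0.20 × 100 = 20 ml to 0.20 × 200 = 40 ml, or 10% to 20% of the 200 ml target.
- Standard error of the difference, without baseline adjustment: 570 × √(2/172) = 61.5 ml.
- With no true effect and an artefact b, type I error = Φ(b/61.5 − 1.96) + Φ(−b/61.5 − 1.96).

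| Assumed artefact b | Type I error |
| --- | --- |
| 0 ml | 0.050 |
| 25 ml | 0.069 |
| 50 ml | 0.129 |
| 100 ml | 0.370 |

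The table shows how sensitive the test would be to an artefact. It does not estimate one.

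**The case against.** The strongest reply is that the protocol is open about its staff. It says that delivering staff are told the arm and claims blinding only for the RRA, residents and relatives. That is right. A reader might infer that outcome assessment as a whole is not blinded as claimed; the documents support this doubt only for the RRA.

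Other stronger readings are also unsupported:

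- *The delivering nurses themselves rate the staff outcomes and collect the pads.* Table 1 names grades and care home staff in general. The same grade is not the same person.
- *The RRA has to question the delivering staff.* Section 7.3.1 offers the participant or proxy as an alternative.
- *Any bias must favour TPTNS.* That direction is plausible, but nothing in the protocol establishes it.
- *Allocation leaks through the Trial Office, which passes it on and also handles data.* Section 6.6 says only: "Staff in the Trial Office work closely with local RRAs to ensure the data are as complete and accurate as possible". Nothing shows that whoever deals with the RRAs on data knows the arms, and no weight is placed on this.

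The primary outcome also has real protection. The RRA weighs and counts the pads, residents are blinded by the sham, a bladder diary runs at each time point, and completeness of the pad test is a pilot progression criterion. Section 4.7 gives diary and photograph checks to the Implementation Support Facilitator, so the RRA has no routine need of the diaries. An artefact of 20 to 40 ml would be less than one standard error.

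These points narrow the finding but do not remove it. None of them shields the RRA during the safety tasks, and none would show that a pad was missing.

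**Conclusion.** The point holds in a limited form, with medium confidence. Section 4.5 states a blinding aim for the RRA that Sections 7.3.1 to 7.3.3 do not protect, and these need to be reconciled. Separately, S-PBC, the staff MTSQ and pad collection depend on staff who may know the allocation, with no rule or record of whether they delivered the treatment.

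The size of any bias is unknown and its direction is not established. The figures of 20 to 40 ml and the type I error table rest on assumed values. No sample size figure changes. The conclusion rests on two judgements: that intensity or electrode site would often identify the arm to an informed reader, and that raters and deliverers will overlap in at least some homes. It should be corrected because the trial adopted a sham in order to blind and the remedies are small.

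**What to change.** 1. **Reconcile Section 4.5 with Sections 7.3.1 to 7.3.3.** Give the questioning of delivering staff, and the review of event records and diaries, to the local PI or a delegate other than the RRA. Leave relatedness to the chief investigator, who is already named for it. Do not move relatedness to the local PI, who holds the allocation. The opening sentence of Section 7.3.3 also lists the RRA and needs the same edit. State that the RRA sees no stimulation diary or electrode-site detail before a visit's outcomes are recorded.
2. **Record rater involvement.** Add a CRF item asking whether the person rating S-PBC or the staff MTSQ delivered that resident's stimulation. Use a rater who did not where feasible; otherwise report these outcomes as unblinded. An absolute rule would be hard to keep in small homes and could replace the carer who knows the resident best.
3. **Reconcile pads.** Count the pads issued for each 24-hour test against those bagged, and record any discrepancy.

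The cost is protocol and CRF wording, slightly more work for the local PI and the chief investigator, and a short pad count at each test.

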**6.2 Baseline**

The RRA will complete the Case Report Form (CRF) for baseline data, which will record:

- Barthel Index (Mahoney & Barthel, 196560)
- Mini Mental State Examination [MMSE] (Folstein et al, 197561)
- Clinical Frailty Scale [CFS] (Rockwood, 200564)
- Continence history and status, including Minnesota Toileting Skills Questionnaire [MTSQ] 65) and current treatment
- Falls and fractures, treated UTIs, emergency admissions to hospital in the previous 6 months
- Pressure ulcer risk and incidence in previous month
- 24 hour PWT
- Number of pads used in 24 hours
- PVRU volume measurements
- Resource Use Questionnaire
- Patient Perception of Bladder Condition
- Family Carer Perception of Bladder Condition
- Staff Perception of Bladder Condition
- DEMQOL
- DEMQOL-proxy
- 24-hour bladder diary information

**6.3 Follow-up**

***6 weeks post randomisation (Primary outcome point)*** (completion of TPTNS/sham programme):

The RRA will complete the CRF including:

- 24 hour PWT
- Number of pads used in 24 hours
- 24-hour bladder diary information
- MTSQ
- Continence status and current treatment
- PVRU volume measurements
- Resource Use Questionnaire
- Patient Perception of Bladder Condition
- Family Carer Perception of Bladder Condition
- Staff Perception of Bladder Condition
- DEMQOL
- DEMQOL-proxy

***12 weeks post randomisation:***

The RRA will complete the CRF including:

- 24 hour PWT
- Number of pads used in 24 hours
- 24-hour bladder diary information
- MTSQ
- Continence status and current treatment
- PVRU volume measurements
- Patient Perception of Bladder Condition
- Family Carer Perception of Bladder Condition
- Staff Perception of Bladder Condition

***18 weeks post randomisation:***

The RRA will complete the CRF including:

- 24 hour PWT
- Number of pads used in 24 hours
- 24-hour bladder diary information
- MTSQ
- Continence status and current treatment
- PVRU volume measurements
- Patient Perception of Bladder Condition
- Family Carer Perception of Bladder Condition
- Staff Perception of Bladder Condition
- DEMQOL
- DEMQOL-proxy
- Resource Use Questionnaire

**6.4 Capture of data from medical records**

Baseline data on medical condition is recorded from the residents medical and care records by the RRA after obtaining consent to participate, prior to randomisation. Data captured includes:

- Biographical information
- Medical history
- Current medication

**6.5 Change of Status/Withdrawal procedures**

Participants remain in the trial unless they (or their welfare attorney/nearest relative [Scotland]) choose to withdraw consent, or if their personal or nominated consultee (England) advises that they believe the person’s wishes about participation have changed or they are unable to continue for a clinical reason or if they die. All changes in status, with the exception of complete withdrawal of consent, mean the participant is still followed up for all trial outcomes wherever possible. All data collected up to the point of complete withdrawal is retained and used in the analysis.

If participants withdraw from the intervention or sham they (or their consultee [England] / welfare attorney/nearest relative [Scotland]), are asked to consider if they wish (the resident) to remain in the trial and be followed up as per trial schedule. Participants (or their consultee [England] / welfare attorney/nearest relative [Scotland]) who wish to withdraw from active trial follow-up are asked if they wish to allow routine follow-up data from CH records to be used for trial purposes.

If an individual CH wishes to withdraw from the study the permission of every participating resident (or their consultee [England] / welfare attorney/nearest relative [Scotland]) must be gained prior to CH withdrawal taking place.

